### Limitations

This study is subject to the inherent limitations of observational studies, including selection bias, information bias, confounding due to informative missing data (e.g., malignant diseases), confounding by indication, and residual confounding due to unmeasured variables. In terms of propofol use, confounding by indication is highly relevant. The main confounding factor is the concurrent use of MV, which indicates underlying respiratory dysfunction. This could lead to an erroneous association between propofol use and a worse outcome, when in fact the worse outcome is caused by the respiratory dysfunction. To minimize this bias, all models will adjust for the concomitant duration of MV in propofol-related associations. Another confounding factor is the use and dosing of propofol in end-of-life care. To minimize this bias, sensitivity analyses will be performed that exclude suspicious state transitions and events occurring close to the last day of propofol therapy (lag time).

Due to the characteristics of our database, we do not have information on concomitant central nervous system dysfunction (e.g., septic *delirium*) in the absence of MV use. This type of organ dysfunction may also require propofol administration and may also be associated with a worse outcome. We have attempted to account for at least some of this bias by adjusting propofol-related associations with the outcome for baseline APACHE II scores (which contain information on the Glasgow Coma Score) and the sepsis admission diagnosis.

Another limitation is that we will be unable to analyze state transitions (multistate models) occurring within 24 hours due to missing information. Furthermore, as propofol data collection ended on day 11 after ICU admission, transition hazards can only be evaluated up to this point, and associations of propofol use with outcomes can only refer to this therapeutic period. However, as recent randomized studies (e.g., SPACE III) only recorded interventional sedation for a median of 2.6 days (IQR 1.10 - 5.3 days),^(30)^ we believe that the maximum therapeutic period (up to day 11 after ICU admission) should provide sufficient time to draw meaningful conclusions about propofol use.

Patients had not been followed after hospital discharge. Therefore, hospital discharge is treated as an endpoint, with in-hospital death as a competing event, and is accounted for using competing risks modeling (cause-specific and Fine and Gray approaches).

### Strengths

The major strength of this study is the large number of patients presenting with a wide range of diseases, enabling broad generalization of the results. Furthermore, our detailed statistical analysis plan enables us to consider two time-dependent variables (the use of propofol and MV) simultaneously, which is a common and serious limitation in observational studies.

### Ethics and dissemination

Institutional ethical approval was granted by the Health Sciences Research Ethics Board at Queen's University, Kingston, Ontario (File No: 6004791, Title: Improving the Practice of Nutrition Therapy in the Critically Ill: An International Quality Improvement Project; Initial approval: 2006/10/10).

Patients’ identities will be kept confidential and will not be disclosed or published under any circumstances, and all legal requirements for the protection of personal data will be observed. Patient data collected in the study will be documented pseudonymously using de-identified patient ID codes. All parties involved in data management and analysis will have access only to non-identifiable patient data.

In addition to this publication, details of the analysis of nutritional data (including fat intake) from the current database have been made publicly available through trial disclosure databases (ISRCTN1; ID number ISRCTN17829198).

To date, this cohort study represents the most extensive data collection of real-world evidence relevant to clinical nutrition and its impact on clinical outcomes in critically ill patients with an ICU LOS > 2 days treated in international ICUs. We therefore plan to disseminate the results at national and international conferences and submit for publication, with authorship following ICMJE recommendations (https://www.icmje.org). In addition, it is also planned that the results will be presented at local congresses and published in national journals.

## Data Availability

All data collected during the study were recorded by designated site personnel in a dedicated repository and stored in a study-specific database.

## Appendix A

Calculation of mg propofol from propofol calories in the context of a simultaneous use of propofol 1% and 2% (the ratio between those two in relation to their respective uses is assumed to be 1: 1.8):

(I)
$$\begin{array}{l} \text{Total propofol calories}\left[{\text{C}}_{\text{Pt}}(\text{kcal})\right]\text{are the sum of calories from propofol}1\text{\%}\left[{\text{C}}_{\text{P}1\text{\%}}(\text{kcal})\right]\text{and propofol}2\text{\%}\left[{\text{C}}_{\text{P}2\text{\%}}(\text{kcal})\right]\\ {\text{C}}_{\text{Pt}}(\text{kcal})={\text{C}}_{\text{P}1\text{\%}}(\text{kcal})+{\text{C}}_{\text{P}2\text{\%}}(\text{kcal}) \end{array}$$

(II)
$$\begin{array}{l} \text{Since}1\text{ml propofol contains}1.1\text{kcal, we can convert calories in ml of propofol}1\text{\%}\left[{\text{P}}_{1\text{\%}}(\text{mL})\right]\text{and propofol}2\text{\%}\left[{\text{P}}_{2\text{\%}}(\text{mL})\right]\text{:}\\ {\text{P}}_{1\text{\%}}(\text{mL})={\text{C}}_{\text{P}1\text{\%}}(\text{kcal})/1.1 \end{array}$$

(III)
$${\text{P}}_{2\text{\%}}(\text{mL})={\text{C}}_{\text{P}2\text{\%}}(\text{kcal})/1.1$$

Since 1mL of propofol may contain either 10mg or 20mg of propofol, we can calculate concentration-specific amounts of propofol [P_1%_ (mg) and P_2%_ (mg)]

(IV)
$${\text{P}}_{2\text{\%}}(\text{mg})={\text{P}}_{2\text{\%}}(\text{mL})\times 20$$

(V)
$${\text{P}}_{1\text{\%}}(\text{mg})={\text{P}}_{1\text{\%}}(\text{mL})\times 10$$

Furthermore, we know that total propofol [P_t_ (mg)] must be the sum of P_2%_ (mg) and P_1%_ (mg)

(VI)
$${\text{P}}_{2\text{\%}}(\text{mg})+P_{1\text{\%}}(\text{mg})={\text{P}}_{\text{t}}(\text{mg})$$

We also know that the ratio between P_2%_ (mg) and P_1%_ (mg) is 1.8: 1

(VII)
$${\text{P}}_{2\text{\%}}(\text{mg})/{\text{P}}_{1\text{\%}}(\text{mg})=1.8$$

From (VI) and (VII) we derive

(IIX)
$$2.8\times {\text{P}}_{1\text{\%}}(\text{mg})={\text{P}}_{\text{t}}(\text{mg})$$

Combining equations (II) to (IIX) in equation (I) yields

C_Pt_ (kcal) = [P_t_ (mg) x 1.8 × 1.1] / [2.8 × 20] + [P_t_ (mg) x 1.1] / [2.8 × 10]

Or P_t_ (mg) = 13.5 x C_Pt_ (kcal)

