#### Data collection

Using a secure web-based data collection tool, the following information was collected: date of ICU admission, admission category (elective surgery, emergency surgery, and medical), primary admission diagnosis (nine categories), sex, age, BMI, daily use of MV/propofol therapy, and Apache II score on the day of admission. Attending physicians or allied healthcare professionals with expertise in nutrition practices (e.g., dietitians) also recorded daily protein intake and route of additional caloric intake (enteral nutrition, parenteral nutrition). For the first 11 days after ICU admission, the database contains information on protein and energy intake, as well as the number of days on which a patient received parenteral nutrition or oral feeding at any time.

Daily propofol-associated energy intake was also collected from the day of ICU admission (partial day) to a maximum of 11 additional days after admission. Information on the exact dose of propofol (administered via 1% or 2% solutions) was not available in the database. However, as propofol-associated energy intake is closely related to the dose of propofol, propofol-associated energy intake can be used as a surrogate parameter for this dose (1mL of a solution containing propofol contains 50mg of soybean oil, and 50mg of purified egg phosphatide, equivalent to 1.1kcal/mL).

Patients were followed in the hospital for a maximum of 60 days after ICU admission. We recorded the time to in-hospital death or discharge alive. Patients who remained alive in the hospital for more than 60 days were considered censored for both risks at that time.

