### Statistical analysis plan

#### Descriptive analysis

Continuous variables are described by mean, SD, median, minimum, and maximum values. In addition, two-sided 95%CIs are calculated for continuous variables. Additional descriptive statistics may be calculated as needed (e.g., quartiles, coefficient of variation, etc.). In particular, the median and interquartile range (IQR) are used to describe non-normally distributed data. Frequencies and corresponding percentages per class level describe categorical variables. Patients with missing data will be excluded. However, we will examine where and how frequently missing values occur in the data overall, how often they co-occur across variables, and whether there are notable patterns of missingness across groups. We will then derive possible limitations of this study from that analysis.

For the competing risk analyses (time-to-discharge alive, time to in-hospital death), we will classify daily propofol-associated energy intake using three thresholds that define three different levels based on the amount of propofol-associated energy received. The identification of specific energy thresholds will be based on clinical practice:^(18,19)^ level I: < 1.0kcal propofol-associated energy/kg per day; level II: 1.5 - 4.5kcal propofol-associated energy/kg per day; level III: > 4.5kcal propofol-associated energy/kg per day). Suppose there is a highly uneven distribution of patient days with a given level of propofol-associated energy intake. In that case, energy thresholds may be redefined after preliminary exploratory analysis of these data, but before assessing the association with outcome.

For converting propofol-associated energy intake into mg propofol, we will assume that the use of 1% and 2% propofol in the present study was similar to that in the multinational EuroPN study on medical nutrition therapy (2% propofol: 62%, 1% propofol: 37%, unknown: 1%; unpublished observations of the EuroPN study).^(20)^ From these data, it is possible to convert propofol-associated energy intake into mg propofol. According to Appendix A, the energy levels above would roughly correspond to the following propofol dose levels: level I: < 20mg/kg per day; level II: 20 - 60mg/kg per day; level III: > 60mg/kg per day. These propofol categories, however, will only be used to interpret results. For all statistical analyses, we will use the levels defined above based on propofol-associated energy intake.

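### The mg/kg labels rest on one average conversion factor although the propofol concentration is unknown, and that factor does not quite follow from its own inputs

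*Protocol article*

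**What the plan says.** The Data collection section states that the exact dose, given as 1% or 2% solution, is not in the database. It takes energy as the surrogate, "as propofol-associated energy intake is closely related to the dose of propofol", with either solution "equivalent to 1.1kcal/mL".

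The Descriptive analysis section sets three energy levels (I: <1.0; II: 1.5-4.5; III: >4.5 kcal/kg per day). To translate them into mg it borrows the split seen in another study: "2% propofol: 62%, 1% propofol: 37%, unknown: 1%; unpublished observations of the EuroPN study". It gives the approximate equivalents as <20, 20-60 and >60 mg/kg per day, and says that these serve interpretation only, while all analyses use the energy levels.

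Appendix A derives the factor. It introduces the split as a ratio of use: "the ratio between those two in relation to their respective uses is assumed to be 1: 1.8". Equation VII then treats it as a ratio of drug amounts: "We also know that the ratio between P_2%_ (mg) and P_1%_ (mg) is 1.8: 1". The combined equation is "C_Pt_ (kcal) = [P_t_ (mg) x 1.8 × 1.1] / [2.8 × 20] + [P_t_ (mg) x 1.1] / [2.8 × 10"], and the result is "Or P_t_ (mg) = 13.5 x C_Pt_ (kcal").

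The Subgroup analysis section gives the level I limit as <1.5 kcal/kg per day. The Limitations section does not mention the unknown concentration.

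**The concern.** The study aims to inform safe propofol dosing, and the Introduction frames the gap in mg/kg (95-120 mg/kg per day). Readers will therefore take the results through the mg/kg labels. If the same energy can mean doses a factor of two apart, a finding for level III cannot be placed on the mg/kg scale without the concentration. By the appendix's own constants, 95 mg/kg corresponds to 95 × 1.1/20 = 5.2 kcal/kg with 2% propofol and 95 × 1.1/10 = 10.5 kcal/kg with 1%.

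Separately, the printed factor should be reproducible from the printed split and equation, and it is not.

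**Working it through.** **Inputs.** Energy density 1.1 kcal/mL for either solution (Data collection, Appendix A); 10 or 20 mg/mL (Appendix A); split 62% (2%) to 37% (1%) (Descriptive analysis); ratio 1.8, applied to mg (Appendix A, equation VII); cut-offs 1.5 and 4.5 kcal/kg per day.

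**1. The plan's own factor.** The printed equation gives kcal per mg = 1.8 × 1.1/(2.8 × 20) + 1.1/(2.8 × 10) = 0.03536 + 0.03929 = 0.07464. Its inverse is 13.40 mg/kcal. The printed 13.5 is 0.8% higher and would need a ratio of 1.88.

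**2. The ratio.** 62/37 = 1.68. With the most favourable rounding of the percentages, 62.5/36.5 = 1.71. Neither gives 1.8.

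**3. The factor from 62:37.** Let r be the ratio of 2% to 1%.
- r as a ratio of mg: (1 + r)/[1.1 × (r/20 + 1/10)] with r = 62/37 gives 13.24, which is 2.0% below 13.5.
- r as a ratio of volume: (20r + 10)/[1.1 × (1 + r)] with r = 62/37 gives 14.78, which is 9.5% above 13.5. The mg ratio is then 2 × 1.68 = 3.35.
- r as a ratio of patients or treatment days: no mg ratio follows without a further assumption. Equal mg per day gives 13.24; equal mL per day gives 14.78.

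**4. The single products.** 1% only: 10/1.1 = 9.09 mg/kcal. 2% only: 20/1.1 = 18.18 mg/kcal. Any mixture lies between these.

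**5. The cut-offs in mg/kg per day.**

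| Factor (mg/kcal) | 1.5 kcal/kg | 4.5 kcal/kg |
|---|---|---|
| 13.5, as printed | 20.3 | 60.8 |
| 13.40, printed equation | 20.1 | 60.3 |
| 13.24, 62:37 as mg | 19.9 | 59.6 |
| 14.78, 62:37 as volume | 22.2 | 66.5 |
| 9.09, 1% only | 13.6 | 40.9 |
| 18.18, 2% only | 27.3 | 81.8 |

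Against the label of 60, the single-product values are 41/60 - 1 = -32% and 82/60 - 1 = +36%.

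**6. Ranking.** Within one concentration, energy orders dose exactly. Between 1% and 2%, the patient with more energy is certain to have the larger dose only if the energy intake is more than twice as large. For example, 4.4 kcal/kg of 2% (level II) is 80 mg/kg, while 5 kcal/kg of 1% (level III) is 45 mg/kg.

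**7. Level I.** The limit of 1.0 kcal/kg in the Descriptive analysis section converts to 13.4-13.5 mg/kg with the average factor, and to 9.1 (1%) or 18.2 (2%) with a single product. None of these is the 20 mg/kg on the label. The 1.5 limit in the Subgroup analysis section converts to about 20. With 1.0 as the limit, intakes from 1.0 to 1.5 fall in no level.

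**The case against.** The best defence is that no estimate depends on the factor. Hazard ratios, cumulative incidences and transition probabilities are all computed on energy, the purpose and exposures are mostly worded as energy intake, and the mg categories are described as approximate and interpretive. The missing dose is disclosed and the borrowed split is stated as an assumption. All of this stands, and it limits the point to interpretation. It does not settle the matter, because interpretation is where the dosing aim is met, no range is given, and the Limitations section is silent.

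Four stronger readings are tempting, and the documents do not support them:
- That the arithmetic slips make the mg/kg levels unreliable. They do not: with 13.40 or 13.24 the limits still round to 20 and 60.
- That the mg ratio must be 3.35:1. That follows from a volume split, or from a split of treatment days with equal daily volume. The source figures are unpublished, and the article does not give the unit.
- That every patient received only one concentration. The article does not say so. The 9.1-18.2 bounds hold for mixtures too.
- That energy carries no ranking by dose. It ranks exactly within a concentration and imperfectly across them, and the reversal in the worked example is chosen close to a cut-off.

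**Conclusion.** The point holds as one about interpretation. The unknown concentration makes each mg/kg limit uncertain by about a third in either direction (41 to 82 mg/kg at 4.5 kcal/kg; 14 to 27 mg/kg at 1.5 kcal/kg). This rests only on the article's own constants of 1.1 kcal/mL and 10 or 20 mg/mL. These are bounds for a patient or ICU on a single product. The average over all patients lies between them, at a place that depends on whether the borrowed split applies here.

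The errors in the factor are real but small: 0.8% for the printed equation and 2.0% with 62:37 as mg. The volume reading, which the documents leave open, moves the limits to about 22 and 67 mg/kg. No model result changes under any of these. The two level I limits contradict each other, and one of them contradicts its mg/kg label.

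**What to change.** - Recompute the factor in Appendix A from 62:37, or justify 1.8. State whether the split is by mg, volume, or patients/days, and the assumption that this brings.
- Beside each level, print the mg/kg equivalent with its range from 9.1 to 18.2 mg/kcal. For level II (1.5-4.5 kcal/kg) this is 14-41 mg/kg if 1% and 27-82 mg/kg if 2%.
- Word conclusions as a response to propofol-associated energy (volume), not as a dose response in mg.
- Add the unknown concentration to the Limitations section, and qualify the statement in Data collection that energy is closely related to dose.
- Reconcile the level I limit between the Descriptive analysis section, the Subgroup analysis section and the mg/kg label.

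I would not ask for a refit with a concentration drawn at random for each ICU. It would assume one concentration per ICU, which the article does not state, and draws made without regard to outcome would mainly add misclassification.

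The cost is text changes only, with no new data or models. Statements in mg become less precise.
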